## Abstract

**Background:**

Nowadays, short dental implants are being increasingly applied in extremely resorbed posterior regions. The recent studies have indicated that short implants present a similar success rate to conventional implants. It is assumed that short implants can avoid additional surgical morbidity and are less technically demanding. However, high-quality evidence (≥Ib: evidence from at least one randomized controlled trial) on comparing the clinical outcome of short implants and longer implants combined with osteotome sinus floor elevation (OSFE) technique is limited.

**Methods/Design:**

The proposed study is designed as a prospective single-center, three-arm parallel group, randomized controlled trial. We plan to enroll 150 patients in need of dental implant treatment in the posterior maxilla. The inclusion criteria include: age ≧18 years, partial edentulism in the posterior maxilla for at least 3 months from tooth loss, residual bone height ranging from 6 to 8 mm, sufficient bone width (≥6 mm) in the edentulous region. The patients will be divided into three groups according to a table of random numbers: group 1: short implants (6 mm) alone; group 2: short implants (8 mm) combined with osteotome sinus floor elevation (OSFE); group 3: standard implants (10 mm) combined with OSFE. The assignment will be concealed from the clinical operators until the beginning of implant surgery. The outcome examiners and patients will be kept blinded to the assignment. Implant survival rates, implant success rates, complications, resonance frequency analysis (RFA) measurements, marginal bone level, treatment time and patient-reported outcome (visual analogue scale for intraoperative discomfort and postoperative pain) will be recorded. Clinical re-evaluations will be performed at 12, 24, 36 and 60 months after crown placement.

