## Method/Design

### Overview

The proposed study is designed as a prospective single-center, three-arm parallel group, randomized controlled trial. We plan to enroll 225 patients in need of dental implant treatment in the posterior maxilla. The study (Number [2015]16) has been approved by the Ethics Committee of Shanghai Ninth People’s Hospital, China. In addition, the study has been registered in ClinicalTrials.gov and the identifier number is NCT02350075. The clinical component of the study will be initiated in September 2015 at the Department of Oral and Maxillofacial Implantology, Shanghai Ninth People’s Hospital, Shanghai Jiao Tong University, China.

The systematic health condition of all the participants will be recorded and they should fulfill the following criteria. Before the implant surgery, all patients will receive clinical and radiographic assessment. All patients will be required to receive oral hygiene instructions before implant surgery. Panoramic and periapical radiographs will be taken to assess the initial bone height and width. If necessary, cone-beam computed tomography will be performed.

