### Allocation and blinding

The patients will be divided into three groups using randomization tables allocating the patient a number within a corresponding envelope: group 1: short implants (6 mm) alone; group 2: short implants (8 mm) combined with OSFE; group 3: standard implants (10 mm) combined with OSFE. The assignment will be concealed from the clinical operators until the beginning of implant surgery. The outcome examiners and patients will be kept blinded to the assignment.

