### Surgical procedures

For all the cases, Straumann (Institute Straumann AG, Basel, Switzerland) Standard Plus implants will be placed. Following a mid-crestal incision, a full-thickness mucoperiosteal flap will be reflected. In group 1, 6-mm implants will be inserted according to the manufacturer’s instructions. In group 2, after implant, the site will prepared to a depth of about 1–2 mm away from the sinus floor, a modification of Summers’ OSFE will be performed to elevate the sinus membrane to a depth of 8 mm. In group 3, similar procedures will be performed until the sinus membrane is elevated to a depth of 10 mm. The OSFE procedure has been described in detail previously [16]. After surgery, anti-inflammatory amoxicillin (Xinya Co., Shanghai, China, 500 mg, three times a day for 7 days) and metronidazole (Xinyi Wanxiang, Shanghai, China, 400 mg, three times a day for 7 days) will be used. In addition, chlorhexidine oral rinse (0.12 %) will be prescribed for 60 s two times a day for 14 days. A one-stage protocol will be performed. After a healing time of 3–4 months, an impression will be taken at the implant level. Straumann synOcta titanium abutments will be fixed onto the implants. Porcelain (Ivoclar Vivadent AG, Schaan, Liechtenstein) fused to noble metal (Heraeus Kulzer Corporation, Hanau, Germany) crowns and bridges will be fabricated.

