#### Sample size

The primary outcome is the implant survival rate. The criterion for significance is set at α = 0.05 (type I error) and at β = 0.10 (type II error). The analysis is two-tailed. The survival rate reported by Esposito et al. 2014 (92 % in the longer group and 85.7 % in the short group) is used to estimate the sample size [15]. Forty-two cases per group can result in a power of 80 %. Assuming the dropout rate at 20 %, 50 cases per group and 150 cases in total are finally determined.

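### Residual bone height sets the amount of sinus lift, yet no stratification by it is stated and the written analysis models leave it out

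*Protocol article*

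**What the plan says.** All of this is in the Protocol article.

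- **Allocation.** The abstract (Methods/Design) says "The patients will be divided into three groups according to a table of random numbers". The section Allocation and blinding says "The patients will be divided into three groups using randomization tables allocating the patient a number within a corresponding envelope". Neither mentions strata or blocks, and neither says that allocation is unrestricted.
- **Eligibility.** Inclusion criteria limit residual bone height to 6 to 8 mm. The Overview has radiographs taken before surgery to assess it, so the value is known for every patient.
- **Procedure.** Under Surgical procedures, group 1 has no elevation and the target depth for group 2 is 8 mm. The text for the third group reads: "similar procedures will be performed until the sinus membrane is elevated to a depth of 10 mm".
- **Target size.** Sample size ends with "50 cases per group and 150 cases in total are finally determined".
- **Analysis.** Statistical analysis writes the GEE mean model as a logit with an intercept and indicators for groups 2 and 3 (taking X as the group code, as the formula requires). For VAS it names ANOVA across the three groups. Bone height is in neither.

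**The concern.** Bone height is more than background here. It helps determine what is done to the patient. Within groups 2 and 3 it sets the size of the lift, and in group 1 it sets how much bone remains above a 6 mm implant. It is therefore a plausible predictor of stability, operating time, pain and survival, although the documents give no effect size for any of these. A chance surplus of low-bone patients in one arm would enter the group comparison unadjusted. Even with perfect balance, outcome variation due to height stays in the error term and costs precision. Both could be reduced with a measurement the trial already takes.

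**Working it through.** **1. Lift as a function of height.** Inputs are height 6 to 8 mm (Inclusion criteria) and target depths of 8 and 10 mm (Surgical procedures). Assumption: depth is measured from the crest, so lift = target depth − height.

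| Height | Group 1, bone above a 6 mm implant | Group 2 lift | Group 3 lift |
|---|---|---|---|
| 6 mm | 0 mm | 2 mm | 4 mm |
| 8 mm | 2 mm | 0 mm | 2 mm |

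Within each elevated arm, height moves the lift by 2 mm, as much as the step between the two target depths.

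**2. Likely imbalance in mean height.** The documents give no distribution. Assume uniform on 6 to 8 mm:

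- SD = 2/√12 = 0.58 mm.
- SE of a difference between two arm means at 50 per arm = 0.577 × √(2/50) = 0.115 mm.
- 95 % chance range = ±1.96 × 0.115 = ±0.23 mm.

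Sensitivity:

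- 40 per arm (50 less 20 % dropout): 1.96 × 0.577 × √(2/40) = ±0.25 mm.
- 75 per arm (the Overview's 225 patients instead of 150): 1.96 × 0.577 × √(2/75) = ±0.18 mm.
- Largest possible SD in a 2 mm window (half at 6, half at 8; SD 1 mm), 50 per arm: 1.96 × 1 × √(2/50) = ±0.39 mm.

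**3. The same as a share of low-bone patients.** Assume half the patients are below 7 mm, with 50 per arm. The arms with the most and the fewest low-bone patients differ by 20 points or more in about 14 % of simulated trials. For one given pair of arms it is 5.7 %. Under the uniform assumption the halves average 6.5 and 7.5 mm, so a 20-point gap is 0.20 × 1 mm = 0.2 mm in mean height, consistent with step 2.

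**4. Whether arm size matters.** The plan's figure is 50 per group; 42 × 1.2 = 50.4 probably explains it. If allocation of 150 were unrestricted:

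- SD of an arm's size = √(150 × 1/3 × 2/3) = 5.8.
- P(50/50/50) = 150!/(50!³ × 3¹⁵⁰) = 0.0055, about 0.5 %.
- Relative efficiency of a two-arm comparison = 4ab/(a+b)². For 45:55 it is 9,900/10,000 = 99 %; for 40:60 it is 9,600/10,000 = 96 %.

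The smallest arm would fall below 42 in about 21 % of such allocations, but 42 is no meaningful floor. At 92 % versus 85.7 %, two-sided 0.05 and 80 % power, n = [1.960√(2 × 0.8885 × 0.1115) + 0.842√(0.0736 + 0.1226)]²/0.063² = 391 per group.

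**5. Room for a covariate.** Counting one implant per case at the planning rates, expected failures are 50 × 0.08 = 4 in an arm at 92 % and 50 × 0.143 = 7.15 in an arm at 85.7 %. With one arm at the lower rate the total is 4 + 4 + 7.15 = 15; with two it is 4 + 7.15 + 7.15 = 18. Three slopes (two group, one height) then have about 5 to 6 events each. Drop-outs counted as non-survival would raise the number of events.

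**The case against.** The strongest reply is that an article may leave strata, blocks and covariates to a full protocol or analysis plan that is not shown, and that unstratified randomisation of about 150 patients is a legitimate choice. Randomisation balances height in expectation, eligibility already confines it to 2 mm, and the chance difference is small beside the 2 mm steps between implant lengths. Most of this stands. Silence on stratification alone would be no finding. What remains is that the article does not leave the analysis open: it writes the model out term by term and names the VAS test, and height is absent from both.

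Three stronger readings are tempting and not supported.

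- **A reader might infer that a random-number table cannot deliver 50 per group.** Such a table can be used to build blocks or a list with 50 numbers per arm, and prepared envelopes fit either. The article does not say that allocation is unrestricted.
- **A reader might infer that unequal arms would damage the trial.** They cause no bias and cost about 1 to 4 % of efficiency. The figure of 42 does not reproduce from its stated inputs, so falling below it means little.
- **A reader might infer that the allocation method makes the arms differ in procedure.** They differ by design. The spread of lift within an arm arises under any allocation method, and stratification would balance it across arms without removing it.

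**Conclusion.** The point holds as a minor improvement. Bone height is measured before surgery, is tied to the procedure delivered, and is missing from both stated analyses. The expected imbalance is about ±0.23 mm in mean height at 50 per arm, and no more than ±0.39 mm for any distribution within 6 to 8 mm. The comparison is not biased by the omission; what is lost is protection against chance imbalance and some precision. The size of that loss cannot be given, because the documents do not say how strongly height relates to any outcome. The conclusion rests on reading depth from the crest and, for the ±0.23 mm, on uniform heights. It does not rest on any claim about arm sizes.

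**What to change.** In Statistical analysis, prespecify baseline residual bone height (continuous, mm) as a covariate. In the GEE, enter it at implant level, using the height at each implant's own site. For VAS, replace the ANOVA with an ANCOVA using the height at each patient's lowest-height study site, since a patient may have several implants.

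If the randomisation list can still be changed, generate it in permuted blocks of randomly varying size, stratified by that same lowest-site height (6 to <7 mm, 7 to 8 mm), and say so in Allocation and blinding. Trial status reports recruitment as open, so this part may come too late; the covariate does not depend on it.

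The cost is one extra term in a survival model with few events and, if stratified, a second envelope series, with height read before the envelope is drawn and block sizes withheld from operators. Adjustment in a logit model also makes the odds ratio conditional on height, which the report should state.

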**Discussion:**

The results of the trial will support better decision-making for dental implant treatment in atrophic maxillary ridges. If favorable, the use of short implants may avoid adjunct procedures used for implant insertion, thus reducing operative time, complexity and postoperative discomfort.

**Trial registration:**

Clinicaltrials.gov identifier: NCT02350075 (registered on 17 February 2015).

## Background

Implant treatment in the posterior maxilla is commonly faced with great challenges due to the limited residual bone height (RBH) and poor bone quality [1]. A cone-beam computed tomographic analysis study based on 199 sinuses showed that RBH ≤4 mm was observed in 46.9 % and 48.9 % of edentulous first and second molar sites [2]. Efforts have been made to allow successful implant treatment in atrophic posterior maxillae. According to current evidence, osteotome sinus floor elevation (OSFE) has been proven to be a predictable surgical procedure with a high success rate to vertically increase the bone volume in atrophic maxilla when the RBH ranges from 6 to 8 mm [3]. However, the additional surgical procedure is technically demanding, and may increase postoperative morbidity and the total cost [4].

As an alternative, short implants are being increasingly applied in extremely resorbed posterior regions. The definitions of short implants varied in the literature. Authors defined implant length less than 11 mm [5], 10 mm [6] or 8 mm [7] as short implants. Telleman argued that because an implant could be placed at a different horizontal level, a short implant should be defined as an implant with a designed intrabony length of 8 mm or less [8].

A recent meta-analysis has indicated that short implants present a similar success rate to conventional implants and the implant length is no longer considered a crucial factor in influencing implant success [9]. However, contradictory results are reported when short implants are inserted in the posterior maxilla. A retrospective cohort study of 4591 Straumann (Standard, Standard Plus, Tapered Effect and Bone Level) implants with up to 10-year follow-up showed that short 6-mm implants in the mandibular posterior sites had a high survival rate of 100 %, while in maxillary posterior positions a survival rate of only 87 % was achieved [10]. On the other hand, several studies reported an acceptable clinical outcome (survival rates range from 90.0 % to 98.3 %) using short implants (5 mm, 6 mm and 7 mm) in the treatment of the posterior maxilla with up to 5–10 years follow-up [11, 12].

To our knowledge, three randomized controlled clinical trials compared short implants versus longer implants in combination with OSFE procedures in the posterior maxilla [13–15]. Similar survival rates were reported in short and longer implant groups after a 1-year follow-up. However, the limited sample size (101 patients in Thoma et al. 2015 [14], 41 patients in Gujie et al. 2014 [13] and 30 patients in Esposito et al. 2014 [15]) might lead to insufficient statistical power. In addition, the lateral sinus floor elevation technique was performed in those patients with RBH from 5 to 8 mm, while the OSFE technique might be more suitable from cost-effectiveness considerations. Thus, there is still an urgent need for randomized controlled clinical trials with long-term data and a sufficient sample size to provide more clinical evidence to decide the best treatment options.

Based on these, we are now designing a randomized controlled trial study with a 5-year follow-up trying to answer the research question: which is the best treatment option in atrophic maxilla with RBH from 6 to 8 mm: short 6-mm implants alone or short 8-mm implants combined with OSFE or standard 10-mm implants combined with OSFE?

### Objective and hypotheses

The aim of the study is to evaluate the clinical success and the patient-reported outcome of intraoperative and postoperative pain of short implants (6 mm) alone, short implants (8 mm) combined with OSFE and standard implants (10 mm) combined with OSFE for treating atrophic posterior maxillary ridges of partially edentulous adults. Considered outcomes include implant survival rates, complications, resonance frequency analysis (RFA) measurements, marginal bone level, treatment time and patient-reported outcome (visual analogue scale for (VAS) intraoperative discomfort and postoperative pain)

## Method/Design

### Overview

The proposed study is designed as a prospective single-center, three-arm parallel group, randomized controlled trial. We plan to enroll 225 patients in need of dental implant treatment in the posterior maxilla. The study (Number [2015]16) has been approved by the Ethics Committee of Shanghai Ninth People’s Hospital, China. In addition, the study has been registered in ClinicalTrials.gov and the identifier number is NCT02350075. The clinical component of the study will be initiated in September 2015 at the Department of Oral and Maxillofacial Implantology, Shanghai Ninth People’s Hospital, Shanghai Jiao Tong University, China.

The systematic health condition of all the participants will be recorded and they should fulfill the following criteria. Before the implant surgery, all patients will receive clinical and radiographic assessment. All patients will be required to receive oral hygiene instructions before implant surgery. Panoramic and periapical radiographs will be taken to assess the initial bone height and width. If necessary, cone-beam computed tomography will be performed.

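### The Overview plans to enrol 225 patients, but the Abstract and the sample-size section fix 150; a minor second error is that 50 per group less 20 % drop-out leaves 40, not 42

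*Protocol article*

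**What the plan says.** Three places in the protocol article state the size of the trial.

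- **Method/Design, Overview:** "We plan to enroll 225 patients in need of dental implant treatment in the posterior maxilla".
- **Abstract, Methods/Design:** "We plan to enroll 150 patients in need of dental implant treatment in the posterior maxilla".
- **Sample size:** "Assuming the dropout rate at 20 %, 50 cases per group and 150 cases in total are finally determined".

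The Sample size section reaches its figure from a smaller number: "Forty-two cases per group can result in a power of 80" per cent. The planning survival rates come from a published trial ("92 % in the longer group and 85.7 % in the short group) is used to estimate the sample size"), with a two-sided 5 % level.

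The Missing data section says that the sample size allowed for loss to follow-up. It also says that drop-outs will be counted as nonsuccess or nonsurvival under intention-to-treat.

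**The concern.** The Overview and Abstract sentences are the same apart from the number, so they describe the same quantity and cannot both be right. The Overview figure stands in the paragraph that cites the ethics approval and the registration. The article also reports that the study is open for recruitment. A reader, an ethics committee or a later author checking whether the trial reached its planned size would find two answers that differ by 75 patients.

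The one total that is tied to a calculation, 150, is also not consistent with its own drop-out allowance. The step from 42 to 50 per group is offered as cover for 20 % loss, and it does not provide that cover.

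**Working it through.** **Inputs.** 225 (Overview); 150 (Abstract and Sample size); three arms; 42 per group, 20 % drop-out, 50 per group, 92 % v 85.7 % survival and two-sided α = 0.05 (all Sample size). Equal allocation is taken from the 50 per group.

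**1. Can the two totals be reconciled?**

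- Per group: 225/3 = 75 and 150/3 = 50. Difference in total: 225 − 150 = 75, and 75/150 = 50 %.
- A second drop-out allowance does not bridge them: 150/0.80 = 187.5 and 150 × 1.2 = 180. Going from 225 to 150 would need a loss of 1 − 150/225 = 33 %, a rate given nowhere.
- Counting implants rather than patients does not bridge them. The Overview and the Abstract both say patients. If the cases in the Sample size section were implants, 225 patients with at least one implant each could not supply only 150.
- The article has no second stage, screening allowance or amendment that leads to 225.

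**2. The drop-out step.** The plan's own figure first: 50 per group from 42 with 20 % drop-out.

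- Standard inflation: n/(1 − d) = 42/(1 − 0.20) = 52.5, so 53 per group and 3 × 53 = 159 in total. The stated 50 is not reproduced.
- Multiplying instead: 42 × 1.2 = 50.4, which is close to 50 (51 if rounded up). This may be where 50 came from, but the article gives no formula.
- Forward check: 50 × (1 − 0.20) = 40, two short of 42.
- Loss at which 50 still leaves 42: 1 − 42/50 = 16 %.
- For 75 per group: 75 × 0.80 = 60.

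**3. What the choice of total means for the stated power.** Two-sided comparison of two proportions by the normal approximation, without continuity correction:

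power = Φ{[Δ − 1.96·√(2p̄(1 − p̄)/n)] / √([p₁(1 − p₁) + p₂(1 − p₂)]/n)}

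with Δ = 0.92 − 0.857 = 0.063 and p̄ = 0.8885. At n = 42 this is Φ{(0.063 − 1.96 × 0.0687)/0.0683} = Φ(−1.05) ≈ 0.15.

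| n per group | what it is | power |
|---|---|---|
| 40 | 50 less 20 % | 14 % |
| 42 | stated basis | 15 % |
| 50 | 150 in total | 17 % |
| 60 | 75 less 20 % | 19 % |
| 75 | 225 in total | 23 % |

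The same formula needs 391 per group for 80 % power. The low power is therefore not caused by the 225/150 conflict, and neither total cures it. It appears here only because any corrected total will need a power statement beside it.

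**The case against.** **The target can be inferred.** The section whose job is to set the sample size says "50 cases per group and 150 cases in total are finally determined", and the Abstract agrees. The figure of 225 appears once, in an overview sentence, with no derivation. The natural reading is that 150 is the target and 225 is an uncorrected number. This stands as the likelier reading, but it is an inference: the Overview states 225 without qualification, and nothing in the article withdraws it.

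**The drop-out error hardly matters.** It amounts to two patients per group followed up, or three more to recruit, and about one point of power. The Missing data section also keeps drop-outs in the primary analysis as nonsurvival, so all 50 per group stay in the denominator. Loss then alters the expected survival rates rather than the number analysed. This largely stands, and it makes the point minor for implant survival. The stated arithmetic is still wrong, and the Missing data section relies on it when it says that loss was accounted for.

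**Stronger readings.** A reader might infer that recruitment has no defined end, or that the investigators could choose between 150 and 225 after seeing results. The documents do not support either. The Sample size section presents 150 as final. No interim look is described, the outcome examiners are to be blinded, and the recalls at which survival is recorded run from 12 to 60 months after crown placement. Operators could notice early failures, but nothing documents a choice of total based on them.

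**Conclusion.** The point holds as an error in the text. The Overview's 225 contradicts the 150 in the Abstract and the Sample size section, by 75 patients in total or 25 per group. No reading of the article reconciles them, though 150 is probably what was meant. The per-group figures assume equal allocation, as 50 per group implies.

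The drop-out slip is a minor addition: 40 rather than 42 per group followed up at 20 % loss, with 53 per group (159 in total) needed to keep 42. That multiplication by 1.2 produced the 50 is a plausible guess and not something the article says.

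The power figures of 14 % to 23 % should not be read as the size of this problem. They show that 42 per group does not give 80 % power at 92 % v 85.7 %, which is a separate and more serious defect.

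**What to change.** State one enrolment total in the Abstract, the Overview and the Sample size section, after checking it against the number approved by the ethics committee and the number registered.

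- **If 150 stands:** correct the Overview, and rewrite the Sample size section so that 50 per group gives 40 followed up after 20 % loss (or 42 at 16 % loss).
- **If 225 is operative:** change the Abstract and the Sample size section to 75 per group, with 60 followed up after 20 % loss, and say how 75 was reached.
- **If 42 followed up at 20 % loss is to be kept:** the total is 159, at 53 per group, which matches neither stated figure.

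In each case, restate the power for the chosen number and do not carry over the 80 %. Making the counts agree does not make that claim true. One sentence should also say that drop-outs remain in the primary analysis as nonsurvival, so that the followed-up number is not mistaken for the analysed number.

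The cost is a few lines of wording, plus an amendment to the approval or the registration if the number there differs. Keeping 150 adds no patients; 159 adds 9; if 225 is operative, recruitment is 75 above the Abstract's figure.
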